## Abstract

**Background:**

Compared to the employed, the unemployed are characterized by a substantially worse health status, particularly with regards to mental health. At the same time, conventional offers of prevention and health promotion rarely reach the unemployed. The JOBS Program is a health promotion program that combines job application training with elements of social learning theory and self-efficacy. Randomized field studies in the USA and Finland found significant positive effects on reintegration into the labor market and health amongst the unemployed. In this confirmatory study, we analyze whether the JOBS Program produces similar positive effects for the unemployed in Germany.

**Methods:**

This study is designed as a country-wide, multi-center, non-blinded, two-armed, parallel-group, randomized controlled trial over 6 months. A total of approximately 1500 unemployed, who are willing to participate, are randomly assigned either to an intervention group or a waiting control group with an allocation ratio of 1:1. Guided by a team of two trainers, the intervention group completes JOBS Program Germany in small groups of 8 to 15 unemployed for a period of 1 week in units of 5 h a day. Primary outcome measures are the reintegration into the labor market, self-efficacy, life satisfaction, subjective state of health, depressive symptoms, and psychological distress. Of secondary interest are moderating variables such as socio-demographic characteristics, the duration of unemployment, and the job-search intensity. Outcomes will be repeatedly assessed via computer-assisted telephone interviews at three points in time: immediately before the intervention (pre-test), immediately after the intervention (post-test), and 6 months after the intervention has ended (6-months follow-up).

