### Specific objectives

The objective of this study is to investigate the effects of the JOBS Program intervention on the reintegration into the labor market, life satisfaction, state of health, depressive symptoms, and psychological distress among the unemployed in Germany. Of secondary interest are moderating factors such as socio-demographic characteristics, the duration of unemployment, and the job-search intensity.

We will compare the reintegration into the labor market and mental health amongst unemployed, who will be randomly assigned to an intervention group that completes JOBS Program Germany, to a waiting control group. The waiting control group will complete JOBS Program Germany only after the trial has terminated.

Given the confirmatory nature of this study, our hypotheses closely resemble those formulated in the respective studies that have investigated the JOBS Program in the US and Finland [10–13]. Compared to the waiting control group, the intervention group is expected to be more often and better reintegrated into the labor market. Moreover, the intervention group is also expected to report higher levels of life satisfaction, to assess its health status more favorably, and to have lower levels of psychological distress and depressive symptoms. More specifically, the following six hypotheses will be tested:

*Hypothesis1*: The JOBS Program Germany will increase the level and quality of reemployment in the intervention group compared to the waiting control group.

*Hypothesis 2*: The JOBS Program Germany will increase self-esteem and self-efficacy and decrease depressive symptoms and distress in the intervention group compared to the waiting control group.

*Hypothesis 3*: The risk of depression, assessed by a high level of depressive symptoms before the JOBS Program Germany, will moderate the effects of the JOBS Program Germany on reemployment and mental health outcomes. The JOBS Program Germany will have stronger employment promoting and mental health effects on those with a higher risk of depression.

*Hypothesis 4*: The job-search intensity, assessed before the JOBS Program Germany starts, will moderate the effects of the JOBS Program Germany on reemployment. The JOBS Program Germany will have stronger employment promoting effects on those with lower initial levels of job-search intensity.

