#### Primary outcome measures

##### Reintegration into the labor market

Reintegration into the labor market will be assessed using a binary indicator of participants’ current employment status (employed vs. unemployed). For those participants who are employed, we will also assess whether they have a fixed-term or a permanent employment contract as well as their weekly working hours. Any subsided labor market activities (e.g., “Mini-Job”) will be assessed, additionally.

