##### Self-esteem and self-efficacy

Participants’ self-esteem is measured with a revised German version of the widely used Rosenberg Self-Esteem Scale [18, 19], for which an internal consistency of Cronbach’s alpha = .84 is reported. Self-efficacy is measured using three short scales for assessing the internal-external control conviction [20], general self-efficacy [21], and generalized self-efficacy expectation [22]. Reliability for the first two scales are reported in terms of McDonald’s omega and lie in the ranges of .53–.73 and .81–.87, respectively. Cronbach’s alpha for the generalized self-efficacy expectation is reported as .74–.94.

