##### Health and health-related outcomes with an emphasis on mental health

We assess life satisfaction with a German version of the Satisfaction with Life Scale (SWLS) [23]. A recent study has tested the psychometric properties of the SWLS in a general population survey in Germany [24]. The results confirm that the SWLS is one-dimensional, and indicate measurement invariance across gender and age. Furthermore, satisfaction with life proofed to be associated with fatigue, the mental health component of quality of life, anxiety, dispositional optimism, pessimism, and sleep quality.

We assess participants’ health status by asking for a self-evaluation of their overall state of health (answers on a 5-point Likert-type Item labeled from “very good” to “very bad”). Additionally, we examine whether participants feel restricted in their everyday activities by chronic health problems. Moreover, we use the Patient-Health-Questionnaire 15 (PHQ-15) to assess the severity of somatic symptoms.

Psychological distress is measured with a short, 21-Item version of the depression-anxiety-stress-scale (DASS-21). Psychometric properties of the DASS-21 (e.g., Cronbach’s alpha = .78–.89) have been assessed in Germany [25] and the DASS-21 has been successfully administered via telephone interviews in various countries [26].

Depressive symptoms are measured using the WHO Well-Being Index (WHO-5) and the Patient-Health-Questionnaire 9 (PHQ-9). The WHO-5 consists of five questions, which assess the subjective well-being. A systematic review, including 213 studies, suggests that the WHO-5 is an adequate instrument for screening depressive symptoms in clinical trials [27]. The WHO-5 has also been successfully applied in the German context [28]. The PHQ-9 module consist of 9 items that are specifically designed to assess depression and have been widely used in clinical contexts as well as in research [29]. It has also been shown that result from the self-administered PHQ-9 are comparable to results for the PHQ-9 administered in telephone interviews [30].

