### Sample size

This trial is conceptualized as a confirmatory study. The respective studies in the US and Finland reported small effect sizes (Cohen’s *d*) ranging from about .14 to .32. for self-esteem, self-efficacy, psychological distress, and depressive symptoms [7, 11]. In order to detect effect sizes of .2, which we deem to be of practical relevance, with 85% power and the conventional alpha-level of .05 (two-tailed t-test), we require a sample size of 450 persons per group. This sample size also allows us to detect a 10 percentage points difference in reemployment with 85% power and alpha-level of .05, assuming a reemployment rate of 30% in the waiting control group. To arrive at our target sample size, we aim at recruiting a total of 1500 unemployed, assuming a dropout rate of 60% between the pre-test (*t*_*0*_) and the 6-months follow-up (*t*_*2*_). We further expect about 60% of the unemployed who attend the information event to participate in our study, resulting in an estimated 2500 unemployed who attend an information event. We summarize our assumptions about response rates and panel attrition in Table 1.

**Table 1 Tab1:** Assumptions about number of participants, response rates, and panel attrition

	Information Event	Allocation/Pre-Test	Post-Test	6-months follow-up
	*-t*_*1*_	*t*_*0*_	*t*_*1*_	*t*_*2*_
Response rate (per cent)		60%	80%	75%
Intervention group (n)	2500	750	600	450
Waiting control group (n)		750	600	450
Total (n)	2500	1500	1200	900

Notes: -*t*_*1*_: 4–5 weeks before JOBS Program Germany; *t*_*0*_: pre-test interview and randomization within 1–2 weeks before JOBS Program Germany; *t*_*1*_: post-test interview within 4 weeks after JOBS Program Germany; *t*_*2*_: second post-test interview (follow-up) 6 months after JOBS Program Germany

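### Six co-equal primary outcomes (seven with self-esteem), several with unranked measures, and no lead outcome, primary time point or success rule; the sample size allows nothing for multiplicity

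*Protocol article*

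**What the plan says.** Under Specific objectives the protocol article declares its status: "Given the confirmatory nature of this study, our hypotheses closely resemble those formulated in the respective studies". It continues: "More specifically, the following six hypotheses will be tested". Hypotheses 1 and 2 concern main effects. Hypotheses 3 to 6 concern moderators, which the article already describes as of secondary interest.

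The abstract lists six primary outcomes without ranking them: "Primary outcome measures are the reintegration into the labor market, self-efficacy, life satisfaction, subjective state of health, depressive symptoms, and psychological distress". The section Primary outcome measures is wider:

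- **Employment:** "Reintegration into the labor market will be assessed using a binary indicator of participants’ current employment status (employed vs. unemployed"), with contract type, weekly hours and subsidised work recorded as well.
- **Self-esteem,** which is not in the abstract's list: "Participants’ self-esteem is measured with a revised German version of the widely used Rosenberg Self-Esteem Scale".
- **Self-efficacy:** "Self-efficacy is measured using three short scales".
- **Life satisfaction:** the SWLS.
- **State of health:** an overall self-rating, an item on restriction by chronic problems, and the PHQ-15.
- **Psychological distress:** the DASS-21.
- **Depressive symptoms:** "Depressive symptoms are measured using the WHO Well-Being Index (WHO-5) and the Patient-Health-Questionnaire 9 (PHQ-9").

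Statistical methods describes a separate t-test or test of proportions for each outcome, plus regression models. Interim analyses applies the same methods at t1 and says the results will not change the trial. The only significance level is in Sample size: "the conventional alpha-level of .05 (two-tailed t-test"). It is used for d = 0.2 and again for a 10-point difference in reemployment. Table 1 reaches 450 per group at t2.

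**The concern.** A confirmatory trial has to fix in advance which result, on which measure and at which time, will count as confirmation. Here the primary set is fixed, but as a list of equals whose membership changes between sections, and with no rule for combining the results. Hypothesis 2 alone covers four constructs.

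The article itself shows that the open choices matter. Under Procedure it reports that earlier studies of the programme found positive or no effects depending on the follow-up interval and the outcome examined, and that some early effects had gone by one year. The Discussion links a positive result to regular, long-term implementation in Germany. That decision should not rest on a set of tests whose overall error rate is unknown.

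**Working it through.** **1. Reproduce the sample size.** Inputs from Sample size: d = 0.2, two-sided alpha 0.05, power 85%.

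n per group = 2 × (1.960 + 1.036)² / 0.2² = 449 by the normal approximation. The exact t-test gives 449.9, so 450. For 30% versus 40% reemployment the requirement is 407 per group (427 with continuity correction), and 450 give 88.3% power. The stated 450 is therefore right at an unadjusted 0.05 and contains no allowance for multiplicity.

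**2. Count the primary measures.** Outside employment there are 1 (self-esteem) + 3 (self-efficacy and control) + 1 (SWLS) + 3 (health) + 1 (DASS-21) + 2 (depressive symptoms) = 11. Employment adds 1 to 4, giving 12 to 15. This count includes single items; nine of the measures are multi-item scales.

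**3. Chance of at least one false positive when there is no effect.** Two assumptions are needed: each test is run at two-sided 0.05, and any one success counts. For k independent tests the chance is 1 − 0.95^k. Counting only false results in the programme's favour it is 1 − 0.975^k.

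| Tests | Either direction | Favouring the programme |
|---|---|---|
| 6 | 26.5% | 14.1% |
| 7 | 30.2% | 16.2% |
| 12 | 46.0% | 26.2% |
| 24 (12 at t1 and t2) | 70.8% | 45.5% |

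Outcomes measured in the same people are correlated. The documents give no correlations, so a range of 0.3 to 0.7 between outcomes was assumed (simulated equicorrelated normal statistics, 200,000 runs):

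| Tests | Either direction (0.3 to 0.7) | Favouring the programme (0.3 to 0.7) |
|---|---|---|
| 6 | 24% to 16% | 12% to 8% |
| 12 | 40% to 23% | 20% to 12% |
| 12 at t1 and t2* | 61% to 36% | 33% to 18% |

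*Correlation of 0.5 to 0.7 assumed between the two time points of the same outcome.

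The nominal values for a single test are 5% and 2.5%. Even the most favourable row is about three times nominal.

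**4. Power if the error is controlled across six outcomes.** The strictest Holm step uses 0.05/6 = 0.0083, critical value 2.638.

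- d = 0.2: 0.2 / √(2/450) = 3.000, and Φ(3.000 − 2.638) = 64%.
- Detectable effect at 85% power: (2.638 + 1.036) × √(2/450) = 0.245.
- 30% versus 40% reemployment: the standard error is √(2 × 0.35 × 0.65 / 450) = 0.0318 under no difference and √((0.21 + 0.24)/450) = 0.0316 under the alternative. Φ((0.10 − 2.638 × 0.0318) / 0.0316) = 69%.

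If self-esteem is kept, making seven outcomes, the step is 0.05/7 = 0.0071 (critical value 2.690). Power for d = 0.2 is then Φ(3.000 − 2.690) = 62%, and the detectable effect is (2.690 + 1.036) × √(2/450) = 0.248.

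**The case against.** The strongest reply is that the analysis plan is not shown and multiplicity control is often placed there. The 0.05 appears only in the sample size paragraph, and Statistical methods states no test-level alpha. This stands in part: the lack of a named correction is not itself the finding, and it is an inference that each primary outcome will be tested at 0.05. But the choice of primary outcomes belongs to the protocol, and this one makes it. If an unseen plan splits alpha six ways, the 85% in Sample size no longer holds at the split level. Either the error rate or the stated power needs correcting.

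A reader might infer that any single significant result would be claimed as confirmation. The article does not say so. The Discussion speaks of reemployment and (mental) health together, Hypothesis 2 is worded jointly, and the dissemination plan commits to reporting all results. No rule excludes the any-one reading, but none adopts it.

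A reader might also infer that a false confirmation is more likely than not. That is not supported. Among the independent-test figures only the 24-test count exceeds 50%. It assumes independence, which is not credible for these scales, and it treats t1 as equal to t2, although the article calls the t1 analysis interim and sizes the trial on t2. It also counts false results in both directions. The wider counts include employment details recorded only for those in work, and the reference to additive indices may mean one index for depressive symptoms.

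**Conclusion.** The point holds in a limited form. The primary set is badly fixed for a confirmatory trial: six outcomes in the abstract, seven in the body, competing measures within three domains, and no lead outcome, primary time point or success rule in the text shown. Testing six outcomes at 0.05 with any one sufficing would give a familywise error of about 16% to 26%, or 8% to 14% for false results favouring the programme. It would be higher if more measures or both time points counted. These figures rest on the two inferences above and on assumed correlations. What needs no assumption is that 450 per group match an unadjusted 0.05 and leave no allowance for multiplicity. The moderator hypotheses are not part of the problem. The change should be made before outcome data are analysed.

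**What to change.** Amend the protocol and the registry entry, by the route the article already provides for amendments:

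1. Name t2 as the primary time point, since Table 1 sizes the trial on it.
2. Make the primary list agree across the abstract, Specific objectives (whose objective sentence omits self-efficacy) and Primary outcome measures, and decide openly whether self-esteem is primary.
3. Name one measure per primary domain.
4. Control the familywise error across that set at two-sided 0.05. Holm is one suitable method; a fixed order or another valid procedure would also serve. State what pattern of results will count as confirmation.
5. Label the remaining measures and all t1 comparisons secondary.
6. Restate the power in Sample size for the chosen procedure. For six outcomes under Holm, the strictest-step figures at 450 per group are about 64% for d = 0.2, 85% for d = 0.245, and about 69% for 30% versus 40% reemployment.

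The cost is the lower stated power; no extra enrolment is required. The detectable 0.245 still lies within the 0.14 to 0.32 range that the article cites from earlier studies. Keeping 85% power for d = 0.2 under a six-way Bonferroni split would instead take about 676 per group.

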**Discussion:**

This confirmatory study will provide empirical evidence on the effectiveness of the JOBS Program on the reintegration and (mental) health of the unemployed in Germany. If our results from the randomized controlled trail in a country-wide field experiment confirm its effectiveness, the JOBS Program Germany could, perspectively, be implemented into the German employment promotion and social security system on a long-term basis.

**Trial registration:**

German Clinical Trials Register (DRKS), DRKS00022388. Registered on 20 July, 2020.

## Background

Unemployment poses a problem for society as a whole and, in particular, a challenge for prevention and health promotion programs. Meta-analyses have shown that compared to the employed, the unemployed have a worse health status [1, 2], particularly with regards to mental health. At the same time, these studies suggest that reemployment fosters mental health. Conversely, poor health decreases the chances of reemployment [3]. Given these interactions between health and unemployment, health promotion is especially important for the unemployed. It is therefore unfortunate that conventional offers of prevention and health promotion rarely reach the unemployed [4].

A promising strategy to meet the challenges of improving the health among the unemployed is interdepartmental cooperation between health promotion and employment promotion. In Germany, the Federal Centre for Health Education (BZgA) and the National Association of Statutory Health Insurance Funds (GKV-Spitzenverband) are currently cooperating with the Federal Employment Agency on a large-scale program called “Linking of Employment Promotion and Health Promotion in the Community Setting”. Within this activity, they have adopted the so-called JOBS Program, which is a preventive intervention program that was originally developed in the 1990s by the Michigan Prevention Research Center [5–7]. The JOBS Program underpins elements of classical job application training with a socio-psychological theoretical foundation of social learning and self-efficacy [8, 9], thus, aiming at both increased employability and preventing negative consequences of unemployment on mental health. At its core, the JOBS Program is a training session (usually 1 week, 5 h a day) that is organized as a workshop in which small groups of unemployed develop job-search skills through active teaching and learning methods. Participants discuss potential setbacks (e.g., application rejections) and develop corresponding coping-strategies while trainers continuously provide additional social support.

Randomized field studies that have evaluated the JOBS Program in the United States [7, 10] and Finland [11] found significant positive effects on reintegration into the labor market and improved health status, such as lower levels of depressive symptoms and psychological distress, among the unemployed who had completed JOBS Program. These positive effects were observed repeatedly in a 6-months follow-up as well as 2 years after the program had ended [12, 13]. Similar results, especially with respect to employment, have been reported for a variation of the JOBS Program in Ireland [14]. A systematic review provides further information on how health promotion for the unemployed has been approached and evaluated [15].

While the positive results from the US, Finland, and Ireland seem promising, it remains an open empirical question whether the JOBS Program will unfold similar effects for the unemployed in Germany. From an international comparative perspective, it should be noted that the success of employment promotion and health promotion among the unemployed probably depends on the country-specific labor market structure and the health and social security systems, respectively. Also, the original JOBS Program was conceived as a preventive measure, primarily for the short-term unemployed, who have recently lost their jobs. In the US study, participants were unemployed for less than 13 weeks; the mean duration of employment in the Finnish study was about 10.7 months and only 28% of the participants had been unemployed for longer than 12 months. In Germany, the proportion of long-term unemployed is particularly high in international comparison. In 2019 about 32% have been unemployed for at least 1 year or longer [16]. Also, the comparatively low levels of education among the unemployed in Germany poses an additional obstacle for reintegration into the labor market.

A randomized control trial in the Netherlands [17] suggests that the positive effects of JOBS Program on the reemployment also apply to the long-term unemployed. More than half of the participants (54%) in the respective study had been unemployed for more than 5 years. The results confirm that JOBS Program fosters reemployment after 12 months among the participants in the intervention group. However, the study did not include measures of physical or mental health.

Against this background, our confirmatory study analyzes whether the JOBS Program increases reemployment and improves health among the unemployed in Germany.

### Specific objectives

The objective of this study is to investigate the effects of the JOBS Program intervention on the reintegration into the labor market, life satisfaction, state of health, depressive symptoms, and psychological distress among the unemployed in Germany. Of secondary interest are moderating factors such as socio-demographic characteristics, the duration of unemployment, and the job-search intensity.

We will compare the reintegration into the labor market and mental health amongst unemployed, who will be randomly assigned to an intervention group that completes JOBS Program Germany, to a waiting control group. The waiting control group will complete JOBS Program Germany only after the trial has terminated.

Given the confirmatory nature of this study, our hypotheses closely resemble those formulated in the respective studies that have investigated the JOBS Program in the US and Finland [10–13]. Compared to the waiting control group, the intervention group is expected to be more often and better reintegrated into the labor market. Moreover, the intervention group is also expected to report higher levels of life satisfaction, to assess its health status more favorably, and to have lower levels of psychological distress and depressive symptoms. More specifically, the following six hypotheses will be tested:

*Hypothesis1*: The JOBS Program Germany will increase the level and quality of reemployment in the intervention group compared to the waiting control group.

*Hypothesis 2*: The JOBS Program Germany will increase self-esteem and self-efficacy and decrease depressive symptoms and distress in the intervention group compared to the waiting control group.

*Hypothesis 3*: The risk of depression, assessed by a high level of depressive symptoms before the JOBS Program Germany, will moderate the effects of the JOBS Program Germany on reemployment and mental health outcomes. The JOBS Program Germany will have stronger employment promoting and mental health effects on those with a higher risk of depression.

*Hypothesis 4*: The job-search intensity, assessed before the JOBS Program Germany starts, will moderate the effects of the JOBS Program Germany on reemployment. The JOBS Program Germany will have stronger employment promoting effects on those with lower initial levels of job-search intensity.

*Hypothesis 5*: The length of unemployment will moderate the effects of the JOBS Program Germany on reemployment. The JOBS Program Germany will have a stronger employment promoting effect for those who have been unemployed for a moderate period compared to (1) the recently unemployed and (2) the long-term unemployed.

*Hypothesis 6*: The length of unemployment will moderate the effects of the JOBS Program Germany on mental health. The JOBS Program Germany will have stronger mental health effects for those who have been unemployed for a moderate period compared to (1) the recently unemployed and (2) the long-term unemployed.

